### General management

2.5 

All other aspects of patient management will be conducted according to standard clinical practice at each participating ICU. This includes, but is not limited to, monitoring of vital signs, laboratory testing, fluid resuscitation, mechanical ventilation, and vasopressor support, as deemed necessary by the attending medical team. No interventions will be applied to any aspect of care other than nutritional support. All concomitant treatments will be determined by the responsible clinicians and documented in the patient’s medical records.

### Study outcomes and their measures

2.6 

#### Primary outcome definition and measures

2.6.1 

Occurrence of FI during the acute phase of critical illness (within the first 7 days of ICU admission) (5). FI is defined as either:

Intolerance to EN due to any clinical reason [e.g., vomiting (any visible regurgitation of gastric content irrespective of the amount), high gastric residual volume (a single volume exceeds 200 ml), diarrhea (having three or more loose or liquid stools per day with a stool weight greater than 200–250 g/day (or greater than 250 ml/day)], GI bleeding [(any bleeding into the GI tract lumen, confirmed by macroscopic presence of blood in vomited fluids, gastric aspirate or stool), etc.,], orFI should be considered present if at least 20 kcal/kg BW/day via enteral route cannot be reached within 72 h of feeding attempt or if enteral feeding has to be stopped for whatever clinical reason.

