### Sample size calculation

2.3 

Sample size calculation was performed using PASS software. The primary clinical outcome was the difference in the incidence of FI between the two groups. Based on previous studies, the incidence of FI among critically ill patients in the control group was assumed to be 0.5. According to the clinical decision curve analysis from the predictive model for FI (NOFI) (10), the net benefit at a threshold probability of approximately 50% was 0.257, indicating that around 25.7 patients out of every 100 would benefit from the intervention. Therefore, it was assumed that the mNEED protocol (intervention group) would reduce the incidence of FI by 25%, resulting in an expected FI rate of 0.375 in the intervention group [0.5 × (1–0.25) = 0.375]. We set the intraclass correlation coefficient (ICC) to 0.10 by analogy to the NEED trial (4), a total of 45 clusters per group were planned, with an ICC of 0.1. Using a two-sided alpha of 0.05 and a statistical power of 90% (1–β = 0.9), the required number of participants per cluster was calculated to be 25. Thus, the total sample size was 45 clusters × 25 participants × 2 groups = 2,250 participants. We pre-specified ICC sensitivity analyses, which indicated that the planned configuration is robust to plausible ICC and cluster-size variability; detailed results are provided in Supplementary Tables 3, 4.

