### Sensitivity analysis using an alternative definition (EFI)

2.6.1.1 

To assess the robustness of the primary outcome, a pragmatic alternative definition of enteral feeding intolerance (EFI) will also be applied in sensitivity analyses. EFI is defined as a clinician’s decision to reduce the prescribed amount of EN specifically because features of gastrointestinal dysfunction appeared during feeding (13). Results derived from this EFI definition will be reported as sensitivity analyses and interpreted only as supportive evidence for the primary outcome, not as separate primary or secondary outcomes.

Since the diagnosis of FI is not completely objective (14), FI was independently adjudicated by two blinded outcome evaluators ([name] and [name]) using a de-identified dataset containing only the prespecified variables (binary gastrointestinal-symptom indicators and 72-h EN delivery data). The evaluators were blinded to treatment allocation and site identities. [name] collated the two assessments; in case of disagreement, he served as the third reviewer and made the final determination. In the final outcome report, all FI cases will be categorized and reported per component as: (i) FI due to gastrointestinal symptom(s), (ii) FI due to inadequate EN delivery, or (iii) both criteria met.

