#### Handling of incomplete FI assessments

2.6.1.2 

(1). If a patient experiences an ICU disposition (death or discharge/transfer) within 7 days of ICU admission, the FI window spans ICU admission to the time of disposition. (2). If no prespecified gastrointestinal (GI) symptom is documented and the patient has an ICU disposition within 72 h of EN initiation such that FI cannot be fully ascertained, the primary analysis will classify the patient as no FI.

Adjusted FI (aFI) sensitivity definition. For the scenario described in rule (2) above, we prespecify an adjusted FI endpoint (aFI) for sensitivity analyses:

If any EN reduction is recorded, classify as FI

If no EN reduction is recorded, classify as no FI.

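### The primary endpoint counts an EN stop for any clinical reason as FI, but the adjudication data cannot score a stop, and non-GI shortfalls within 72 h can still count as FI

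*Protocol article*

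**What the plan says.** Section 2.6.1 observes FI "within the first 7 days of ICU admission" and gives three ways to meet it: a gastrointestinal (GI) symptom or other clinical intolerance; failure to reach 20 kcal/kg/day by the enteral route within 72 h of the feeding attempt; or a stop, which counts "if enteral feeding has to be stopped for whatever clinical reason". Neither the delivery limb nor the stop limb is restricted to a GI cause.

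Section 2.6.1.1 describes how FI is adjudicated. Two blinded evaluators work from a de-identified extract limited to "binary gastrointestinal-symptom indicators and 72-h EN delivery data". Cases are then reported as "i) FI due to gastrointestinal symptom(s), (ii) FI due to inadequate EN delivery, or (iii) both criteria met". The same section defines an alternative, EFI, as a clinician's reduction of EN "specifically because features of gastrointestinal dysfunction appeared during feeding", and makes it supportive only.

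Section 2.6.1.2 covers patients who die or leave the ICU early. With no listed GI symptom, and death or departure within 72 h of EN start so that FI cannot be fully ascertained, "the primary analysis will classify the patient as no FI".

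Section 2.3 states that "the incidence of FI among critically ill patients in the control group was assumed to be 0.5", citing previous studies, and does not say which limbs of FI that rate covers.

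**The concern.** The symptom limb already catches patients with a listed GI symptom. What the stop limb adds is mainly stops without one, such as fasting for a procedure or an interruption around extubation. Whether these patients are events therefore depends on whether and how that limb is applied. Section 2.6.1 says they count; section 2.6.1.1 supplies neither the data nor a category to count them. Two teams following the two sections could reach different primary results from the same records.

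The delivery limb raises a second problem. A patient whose feeding is interrupted within 72 h for a non-GI reason, and who therefore misses the energy target, is an FI case, and adjudicators cannot see why delivery fell short. At stake are what the primary result measures and, if such events are common and beyond the reach of a feeding protocol, its power.

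**Working it through.** **1. Scoring example patients under each section.** None has a GI symptom.

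- EN held on day 2 for a procedure, restarted, 72-h target met. Section 2.6.1, read literally: FI by the stop limb. Extract in section 2.6.1.1: no symptom flag and adequate delivery, so no FI.
- EN stopped for a non-GI reason after 72 h but within 7 days. Section 2.6.1: FI. Extract: outside the 72-h delivery data, so no evident route to FI.
- EN stopped at 60 h for extubation, oral diet follows, patient still in the ICU on day 4, and less than 20 kcal/kg/day of EN reached. Delivery limb: FI under both sections, with no reason asked.
- The same feeding course, but the patient leaves the ICU before 72 h from EN start. Section 2.6.1.2: no FI.

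The first two show the contradiction. The last two show that, for the same feeding course, remaining in the ICU decides the outcome.

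**2. Reproducing the design.** Inputs from section 2.3: 0.50 v 0.375, two-sided alpha 0.05, power 0.90, ICC 0.10, 45 clusters per arm.

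- Individually randomized size: n = [1.96·√(2·p̄(1−p̄)) + 1.2816·√(p0(1−p0)+p1(1−p1))]² / (p0−p1)². With p̄ = 0.4375 this is 329 per arm.
- Cluster size at 45 clusters: m = n(1−ICC)/(45 − n·ICC) = 329×0.9/(45−32.9) = 24.5, rounded up to 25. Total 45×25×2 = 2,250.
- Design effect 1+24×0.10 = 3.4, so effective n per arm = 1,125/3.4 = 330.9.
- Power = Φ[(|p0−p1| − 1.96·SE0)/SE1], where SE0 = √(2·p̄(1−p̄)/330.9) and SE1 = √([p0(1−p0)+p1(1−p1)]/330.9). Result 0.902.

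The planned figures reproduce, so the sample-size arithmetic is not at fault.

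**3. Dilution, events on top of the planned rates.** Assumption: a share q of patients otherwise free of FI has a non-GI event scored as FI, equally in both arms. The documents give no q. Then p′ = p + (1−p)q and the difference becomes 0.125(1−q). At q = 10%, control is 0.50+0.50×0.10 = 0.55 and mNEED is 0.375+0.625×0.10 = 0.4375.

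| q | Control | mNEED | Difference | Power, 45×25 per arm | Power, 54×25 per arm | Power, 54 ICUs per arm, total 2,250 |
|---|---|---|---|---|---|---|
| 0 | 0.500 | 0.375 | 0.125 | 0.902 | 0.946 | 0.935 |
| 5% | 0.525 | 0.406 | 0.119 | 0.866 | 0.920 | 0.906 |
| 10% | 0.550 | 0.4375 | 0.1125 | 0.826 | 0.888 | 0.872 |
| 20% | 0.600 | 0.500 | 0.100 | 0.735 | 0.810 | 0.789 |

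The 54 ICUs per arm come from section 2.4.1.

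**4. Two other readings of the 0.50.**

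- It already contains a fraction q of all patients with non-GI events, and the 25% reduction reaches only the rest. The mNEED rate is q + 0.75(0.50−q) = 0.375+0.25q, that is 0.388, 0.400 and 0.425 at q = 5%, 10% and 20%. Power at 45×25 is 0.831, 0.735 and 0.490.
- The 25% reduction applies to the endpoint exactly as defined. Power stays 0.902.

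**The case against.** A reader might infer more: that every procedural fast, extubation or move to oral diet scores as a primary event, so the trial is underpowered. The documents do not support that.

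- The extract that hides the reason for a stop also gives the stop no evident route to being scored. A brief hold with the target met, or a non-GI stop after 72 h, would not be an event under section 2.6.1.1. Section 2.4.2 does mention review of daily feeding data, which could show days without EN, but it mentions no reasons.
- Feeding that has to be stopped does not plainly include an elective change to oral diet. That patient counts, if at all, through the delivery limb.
- The power loss rests on an assumed rate and on one reading of the 0.50. The Introduction treats the 40% of patients in the earlier NEED trial who missed the energy target as FI without asking why, which suggests that shortfalls may already be inside the 0.50. Depending on what the 25% reduction reaches, the loss is then larger or nil.

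The sponsor can also say that section 3.1 discloses the adoption of a 2012 consensus definition, and that component reporting and the EFI analysis are prespecified. These help interpretation, but EFI is supportive only and cannot correct the primary test. The aFI sensitivity definition in section 2.6.1.2 also asks for no reason when EN is reduced.

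Finally, scoring on reasons recorded by sites that know their own feeding protocol could replace roughly equal misclassification with differential misclassification. That objection stands, and it shapes the fix.

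**Conclusion.** The point holds as a contradiction in how the primary endpoint is scored. The stop limb in section 2.6.1 cannot be applied with the data and categories in section 2.6.1.1. Non-GI shortfalls within 72 h can count as FI for a patient who stays in the ICU but not for a similar patient who leaves. This needs no assumption about rates.

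The effect on power is conditional. If such events are equally frequent in both arms, cannot be prevented by the protocol and come on top of the planned rates, an assumed 5% to 20% lowers power at 45×25 per arm from 0.90 to between 0.87 and 0.74. With 54 ICUs of 25 per arm, power is still 0.92 at 5% and 0.89 at 10%. It is unchanged if the 25% reduction applies to the endpoint as defined. The documents do not settle which case applies, so a definite loss of power should not be claimed.

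**What to change.** Before unblinding:

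1. Reconcile sections 2.6.1 and 2.6.1.1 by stating whether non-GI stops and non-GI 72-h shortfalls count as FI, for patients who stay in the ICU as well as those who leave.
2. Add to the blinded, de-identified adjudication extract an EN-stop indicator over the full 7-day window, and the recorded reason for each stop or shortfall.
3. Add a stop category to the component report.
4. Report FI with and without events whose only recorded reason is non-GI. Prespecify one version as primary and the other as a sensitivity analysis.
5. State in section 2.3 which limbs of FI the 0.50 covers.

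The cost is wording, a few variables in the extract and one extra analysis. EFI already requires knowing whether GI dysfunction prompted an EN reduction, so much of the reason information is needed anyway. The downside is that sites that know their own feeding protocol record the reason, so the version that excludes non-GI events is open to differential recording; hence both are reported. Because 108 ICUs were already enrolled by 15 June 2025, the change should be a dated amendment made without sight of results by arm.

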### Sensitivity analysis using an alternative definition (EFI)

2.6.1.1 

To assess the robustness of the primary outcome, a pragmatic alternative definition of enteral feeding intolerance (EFI) will also be applied in sensitivity analyses. EFI is defined as a clinician’s decision to reduce the prescribed amount of EN specifically because features of gastrointestinal dysfunction appeared during feeding (13). Results derived from this EFI definition will be reported as sensitivity analyses and interpreted only as supportive evidence for the primary outcome, not as separate primary or secondary outcomes.

Since the diagnosis of FI is not completely objective (14), FI was independently adjudicated by two blinded outcome evaluators ([name] and [name]) using a de-identified dataset containing only the prespecified variables (binary gastrointestinal-symptom indicators and 72-h EN delivery data). The evaluators were blinded to treatment allocation and site identities. [name] collated the two assessments; in case of disagreement, he served as the third reviewer and made the final determination. In the final outcome report, all FI cases will be categorized and reported per component as: (i) FI due to gastrointestinal symptom(s), (ii) FI due to inadequate EN delivery, or (iii) both criteria met.

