#### Blinding

2.4.2 

Participants or their legal representatives will be completely blinded to group allocation. Healthcare providers will only be aware of the feeding protocol used in their own center and will not be informed of group assignments in other centers. Outcome assessments will be conducted by a dedicated research team that is not involved in the implementation of the feeding protocols and is unaware of the grouping of these patients. For the primary outcome, after the study is completed, GI symptoms and daily feeding data recorded in the database will be reviewed and consolidated by the research team at the coordinating center to perform a unified evaluation. Statistical analyses will also be conducted by researchers at the coordinating center. Emergency unblinding will be permitted in cases of safety concerns or when significant differences in outcomes between groups are observed.

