##### Arm#1 mNEED group

2.4.3.1 

If a center is randomized to the intervention group, training on the implementation of the mNEED nutrition protocol and ultrasound assessment will be conducted before enrolling the first patient. The mNEED protocol includes several modifications to the original NEED protocol:

For patients with AGI ≤ III, the risk of feeding intolerance (FI) is predicted using the NOFI model. Based on the predicted probabilities (< 30%, 30%–85%, and > 85%), different feeding strategies are adopted according to the threshold values identified from the NOFI decision curve analysis.The initial feeding rates have been reduced overall. Instead of the original rates of 25 mL/h for AGI < I and 15 mL/h for AGI II–III, the revised rates are: 20 mL/h for < 30% predicted FI risk, 15 mL/h for 30%–50%, and 10 mL/h for 50%–85%.For AGI ≤ III patients with a predicted FI probability > 85%, early EN (EEN) is deferred, and re-evaluation is performed after 12 h.The FI assessment interval has been extended from 4 to 6 h to every 12 h. Additionally, when the FIS (Feeding Intolerance Score) is 0, the incremental feeding volume has been reduced from 10 to 5 mL/h. The rationale for both adjustments is consistent with the overall strategy: to avoid overly rapid feeding advancement during the acute phase, which increases the risk of FI and early overfeeding.A new item has been added to limit energy provision to no more than 70% of the target caloric intake during the first 3 days, in accordance with ESPEN guidelines, to minimize the risk of early overfeeding.The decision to initiate supplemental parenteral nutrition (SPN) is based on evaluating the patient’s nutritional needs curve. The objective is to align nutritional delivery as closely as possible with this curve, ensuring adequate energy provision while avoiding overfeeding.

To monitor whether enrolled patients are managed in accordance with the study protocol, research staff at each participating center are required to complete a feeding record form for every patient until ICU discharge. This form includes detailed components of the FIS, with evaluations performed every 12 h. It records the FIS values and corresponding adjustments in the feeding rate. Upon study completion, electronic versions of the FIS record forms for all patients will be collected via email.

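### The primary endpoint counts EN stops over 7 ICU days, but the adjudication dataset holds EN data for only 72 h and lists no stop reasons, so some defined FI events would be scored as no FI.

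*Protocol article*

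**What the plan says.** Three places in the protocol article describe how the primary outcome is determined.

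- **Section 2.6.1 (definition).** The window is "Occurrence of FI during the acute phase of critical illness (within the first 7 days of ICU admission"). FI is present on GI intolerance, or "if at least 20 kcal/kg BW/day via enteral route cannot be reached within 72 h of feeding attempt". A further route to FI is that EN is halted: "or if enteral feeding has to be stopped for whatever clinical reason". The 72-hour limit is attached to the energy criterion. The stop criterion carries no time limit other than the 7-day window.
- **Section 2.6.1.1 (adjudication paragraph).** Two blinded evaluators work from a "de-identified dataset containing only the prespecified variables (binary gastrointestinal-symptom indicators and 72-h EN delivery data"). All FI cases are then reported as "i) FI due to gastrointestinal symptom(s), (ii) FI due to inadequate EN delivery, or (iii) both criteria met".
- **Section 2.4.2 (Blinding).** For the primary outcome, "GI symptoms and daily feeding data recorded in the database will be reviewed and consolidated by the research team at the coordinating center", to allow a unified evaluation. No 72-hour limit appears here.

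Section 2.6.1.2 shortens the FI window only for death, discharge or transfer from the ICU. Table 1 shows nutrition delivery and GI symptoms collected repeatedly after allocation.

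**The concern.** An adjudicated endpoint is only as wide as the data the adjudicators hold. Here the definition has a route to FI that can occur on any of the first 7 days, while the adjudicators' EN data end at 72 h. An EN stop on day 6 for a reason outside the GI-symptom flags meets the definition but does not appear in their dataset.

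The same gap exists in milder form before 72 h. The stop criterion turns on a clinical reason, and the listed variables do not include a reason. Delivery data may show that feeding ceased, but not why.

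The primary outcome could therefore be scored differently according to whether the team follows 2.4.2 or 2.6.1.1, and under 2.6.1.1 the endpoint analyzed is narrower than the endpoint defined.

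**Working it through.** **Step 1. Which FI events does the 2.6.1.1 dataset capture?**

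| Route to FI in 2.6.1 | Time limit in 2.6.1 | Visible in the 2.6.1.1 dataset? |
|---|---|---|
| GI symptom | 7 days | Yes; the symptom indicators carry no 72-h limit |
| 20 kcal/kg/day not reached enterally | 72 h from feeding attempt | Yes |
| EN stopped, with a flagged GI symptom | 7 days | Yes, through the symptom flag |
| EN stopped within 72 h, no flagged symptom | 7 days | In part: delivery may fall, but no reason is listed |
| EN stopped after 72 h, no flagged symptom | 7 days | No |

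The full loss is confined to the last row, and within it to patients who reached 20 kcal/kg/day by 72 h. Those who did not are already FI.

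**Step 2. Do the sensitivity analyses recover these events?** No. The adjusted definition (aFI, section 2.6.1.2) applies only to patients with an ICU disposition within 72 h of EN initiation. The alternative definition (EFI, section 2.6.1.1) counts reductions made because of gastrointestinal dysfunction, so a stop for another clinical reason is outside it.

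**Step 3. How much of the window has no EN data?** The 72 h are taken to run from the start of EN, as 2.6.1 and 2.6.1.2 imply. Days without EN data = 7 − (EN start day + 3). The start day is an assumption; the Introduction cites a mean of 1.2 days in the intervention arm of the earlier NEED trial.

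- Start at 1 day: 7 − 4 = 3 days (43%)
- Start at 1.2 days: 7 − 4.2 = 2.8 days (40%)
- Start at 2 days: 7 − 5 = 2 days (29%)

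These are shares of calendar time, not of missed events.

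**Step 4. What could it do to the comparison?** First the plan's own figure from section 2.3: 0.5 versus 0.375, two-sided alpha 0.05, power 90%, ICC 0.10, 45 clusters of 25 per arm.

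- Individually randomized size: 329 per arm.
- Design effect: 1 + (25 − 1) × 0.10 = 3.4.
- Required per arm: 329 × 3.4 = 1,119, against 45 × 25 = 1,125 planned.
- Effective size per arm: 1,125 / 3.4 = 330.9, which gives power 0.902. The plan's figure reproduces.

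Now let x0 (control) and x1 (mNEED) be the shares of patients who are FI only through an unseen late stop. Taking the planned rates as the true rates under the full definition, the scored difference is (0.5 − x0) − (0.375 − x1) = 0.125 + (x1 − x0). The document gives neither share, so the values below are assumptions.

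| x0 (control) | x1 (mNEED) | Scored rates | Scored difference | Power |
|---|---|---|---|---|
| 0 | 0 | 0.500 vs 0.375 | 0.125 | 0.902 |
| 2% | 2% | 0.480 vs 0.355 | 0.125 | 0.905 |
| 5% | 5% | 0.450 vs 0.325 | 0.125 | 0.912 |
| 2% | 5% | 0.480 vs 0.325 | 0.155 | 0.984 |
| 5% | 2% | 0.450 vs 0.355 | 0.095 | 0.703 |

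Equal shares leave the risk difference unchanged. Unequal shares move it in either direction, and nothing in the document says which row applies.

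**The case against.** **Section 2.4.2 already covers daily feeding data.** This is the strongest reply. If the unified evaluation uses daily data, late stops can be seen, and the 72-hour phrase may be a loose summary in a condensed article. This stands to the extent that the fault is a contradiction between sections, not a settled absence of data. It does not remove the fault: 2.6.1.1 is the paragraph devoted to adjudication and says the dataset contains only the listed variables. Section 2.4.2 may describe an earlier consolidation step, and it does not mention reasons for stopping.

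**The stop criterion may be meant to share the 72-hour limit.** It stands in the same sentence as the energy criterion. If that is the intention, the dataset nearly fits, but 2.6.1 does not say so.

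**A stop may belong under inadequate delivery.** Section 2.6.1 places under-delivery and stopping in one limb, so the three reporting classes can accommodate a stop. This largely stands. A fourth class is not required, but the text should say where a stop is counted.

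**Binary flags are not in themselves an error.** The symptom thresholds can be applied when the symptom is recorded. The stool-weight criterion, given as a range, is a separate and minor wording point.

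**A reader might go further and infer a bias toward mNEED**, on the ground that "the incremental feeding volume has been reduced from 10 to 5 mL/h" and that its patients therefore meet full feeding only after the adjudicators' EN data end. The document does not support this, for three reasons.

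- The slower escalation is described relative to the original NEED protocol, not to the control arm. Control ICUs have the same 70% energy ceiling for the first 3 days and no set rate (section 2.4.3.2).
- The time to any given rate depends on body weight and formula density, which the document does not give.
- Where escalation is slow enough to keep a patient under 20 kcal/kg/day at 72 h, that patient is already FI and a later stop changes nothing.

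**Conclusion.** The concern holds in a limited form. Sections 2.4.2, 2.6.1 and 2.6.1.1 do not agree on the data behind the primary endpoint. If 2.6.1.1 is followed literally, patients who reach 20 kcal/kg/day by 72 h, have no flagged GI symptom, and then have EN stopped within the 7-day window for another clinical reason are FI by definition but scored as no FI.

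The EN data would be absent for about 2 to 3 of the 7 days if feeding starts 1 to 2 days after admission. The number of affected patients is unknown and may be small. The size and direction of any bias cannot be determined: a difference between arms is possible but not shown. The sample size calculation is unaffected.

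The point still needs correcting, because it concerns what counts as a primary event and should be settled before adjudication.

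**What to change.** Reconcile 2.4.2, 2.6.1 and 2.6.1.1 by one of two routes, chosen without reference to outcome data by arm.

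1. **Keep the 7-day stop criterion.** Extend the masked adjudication dataset to daily EN delivery through day 7 or ICU disposition, with the date and reason of each EN stop. State which of the reporting components a stop belongs to.
2. **Restrict the stop criterion.** State in 2.6.1 that stops after 72 h do not count toward the endpoint, and still supply the reason for stops within 72 h.

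In either case, 2.4.2 and 2.6.1.1 should describe the same dataset. The stool-weight range can be reduced to a single stated cut-off in the same edit.

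The cost is a wider extract, somewhat more reading per patient and revised wording. Daily nutrition delivery and GI symptoms are already collected. The article does not show whether stop reasons are captured as a separate field, so this must be checked; if they are not, they would have to be taken from feeding or medical records. Free-text reasons would need screening so that they do not reveal the arm.
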